## Abstract

**Background:**

Tuberous sclerosis complex (TSC) is a rare genetic disorder caused by pathogenic variants in the *TSC1* or *TSC2* genes. Apart from multisystem physical manifestations, most individuals with TSC experience TSC-associated neuropsychiatric disorders (TAND). Little is known about how TAND severity changes over time and what factors may predict these changes. Preliminary data suggest the presence of differential TAND severity trajectories. Caregiver well-being may act as a mediator of TAND severity, and a well-being intervention designed for caregivers of children with developmental disabilities may improve caregiver well-being.

**Objective:**

The study aims are to (1) examine longitudinal trajectories of TAND severity in a large sample of individuals with TSC and to examine potential predictors of differential trajectories, (2) evaluate the association between caregiver well-being characteristics, TAND severity, and severity trajectories, and (3) adapt and evaluate the feasibility, acceptability, and potential efficacy of a brief, online group–based well-being intervention for family caregivers.

**Methods:**

For the first 2 aims, 500 individuals with TSC or their caregivers will be recruited in an accelerated longitudinal design to document TAND severity at 5 time points over 12 months via a web-based app. At each time point, participants will complete demographic, TSC characteristics, intervention, and well-being questionnaires. Data will be analyzed using latent class mixed and multinomial regression modeling (aim 1) and structural equation and mediation modeling (aim 2). Participatory methods will be used to adapt an existing caregiver well-being intervention for the TSC community (aim 3). Thirty caregivers will be invited to participate in the adapted group-based online well-being intervention.

**Results:**

This study was funded from July 2024 (HT94252410790 and HT94252410791), and ethics approvals were obtained from the University of Cape Town (July 2024), Vrije Universiteit Brussel (November 2024), and the Department of Defense Office of Human Research Oversight (December 2024). The TAND Toolkit app was adapted for longitudinal data collection (aims 1 and 2). Recruitment started in December 2025 and will continue until 500 participants are enrolled (anticipated December 2026). Primary outputs are expected by July 2028. For aim 3, experiential and adaptation workshops were completed in June 2025, the pilot intervention was delivered in November 2025, and data collection will continue till May 2026. Outputs are expected by December 2026.

**Conclusions:**

Identification of differential longitudinal TAND trajectories and their correlates will stimulate research in TSC and generate evidence for the self-report quantified TAND checklist as a clinical outcome measure. Understanding the association between caregiver well-being and TAND severity will provide support for targeted well-being interventions. A successful pilot trial will provide preliminary data for larger-scale clinical trials, with the potential to support caregivers and improve TAND outcomes. Together, the findings from the study will help close the gap in interventions for TAND.

**Trial Registration:**

ClinicalTrials.gov NCT06879665; https://clinicaltrials.gov/study/NCT06879665

**International Registered Report Identifier (IRRID):**

DERR1-10.2196/91726

## Introduction

### Overview

Tuberous sclerosis complex (TSC) is a rare genetic disorder caused by pathogenic variants in the *TSC1* or *TSC2* genes, leading to overactivation of the mammalian target of rapamycin intracellular signaling pathway [1,2]. With a birth incidence around 1:6000 [3,4], TSC is associated with multisystem manifestations including tumor formation in the skin, heart, kidney, and brain, high rates of epilepsy, and a wide range of TSC-associated neuropsychiatric disorders (TAND) [1,5,6]. The term TAND refers to the broad range of behavioral, psychiatric, intellectual, academic, neuropsychological, and psychosocial difficulties that can occur in people with TSC [6]. While not all individuals with TSC experience every aspect of TAND, the vast majority experience some TAND manifestations across the lifespan and require targeted identification and support [6,7]. TAND has been identified by TSC families as one of the greatest burdens of the disease and highlighted as a top priority for research [6,8,9]. In a Belgian participatory project to identify research priorities, improving access to treatment for TAND was identified as the top priority [10].

Although more than 90% of individuals with TSC have a lifetime history of TAND manifestations [11], very few receive access to diagnostic or interventional services or support. To reduce this gap, the 2012 Neuropsychiatry Panel coined the term “TAND” (1) as an umbrella term for the wide range of bio-psycho-social challenges seen in TSC and (2) to introduce a shared language for clinical practice and research. TAND includes 6 different “levels” of investigation: behavioral, psychiatric, intellectual, academic, neuropsychological, and psychosocial [12]. At the request of TSC stakeholders, a TAND checklist (TAND-Lifetime checklist [TAND-L])—a tool to support clinicians with a systematic screening for TAND across these levels—was developed, pilot validated, and disseminated in the TSC community [13,14].

One of the characteristics of TAND is its highly heterogeneous nature. Some individuals with TSC have many and severe TAND manifestations, while others may have very few [6,11,12,15]. In an attempt to reduce this “overwhelming uniqueness” of TAND (the fact that everyone with TSC seemed to have their own unique TAND profile), data collected by the TAND-L were analyzed using cluster analytic methods in search of natural “TAND clusters” [16-18]. Ward’s cluster analysis, 1000-fold bootstrapping, and exploratory factor analysis were used to identify 7 natural TAND clusters—autism-like, eat/sleep, dysregulated behavior, mood/anxiety, neuropsychological, overactive/impulsive, and scholastic clusters [16-18]. In a next-step project, Alperin and colleagues [11] independently confirmed these natural cluster profiles and extended the field to examine “clusters-of-clusters.” In a sample of >600 individuals with TSC, they described a group of individuals who had difficulties in all 7 natural TAND clusters (“high symptom burden”), a group with no cluster difficulties (“low symptom burden”), and 5 groupings in between these extremes. These studies represented important steps toward reducing the apparent heterogeneity of TAND with implications for clinical practice and research.

Following the development of the TAND-L and identification of natural TAND clusters, participatory research with the TSC community identified the need for a TAND checklist that can be self-reported by families and could quantify TAND severity. Such a checklist could be used in clinical practice and in research to monitor change in TAND over time and potential outcomes from interventions. Family stakeholders asked for the checklist to be built into a smartphone app and for a toolkit of useful tips and information to use at home as “next steps” for action [16,19]. This was the basis for the TANDem-1 project [19].

### From TANDem-1 to TANDem-2: Closing the Gap to TAND Interventions Through Participatory Research

In TANDem-1, the TAND consortium (an international group of TSC clinical research and lived experts with a focus on TAND research [19]) converted the TAND-L to a self-report quantified checklist (self-report quantified TAND checklist [TAND-SQ]) that individuals with TSC or their caregivers could use to document and quantify TAND difficulties themselves [20]. The TAND-SQ was feasible and acceptable to the TSC community, particularly families, who are the primary intended respondents for the TAND-SQ [20]. In the TAND-SQ, a 0-10 severity rating was added to all TAND cluster items, allowing the quantification of TAND difficulties experienced over the past month. Table 1 summarizes the range of TAND severity scores that can be derived using the severity ratings from the TAND-SQ, as proposed by the TAND consortium [21]: an individual item severity score, a mean cluster severity score (CSS_mean_), a maximum cluster severity score, a mean total TAND severity score (TTSS_mean_), and a maximum total TAND severity score (TTSS_max_). The CSS_mean_ has been found to be internally consistent and significantly related to relevant clinical diagnoses and standardized behavioral measures. The TTSS_mean_ has also been found to be a valid indicator of overall functioning and behavior [21].

**Table 1 table1:** Tuberous sclerosis complex–associated neuropsychiatric disorders (TAND) severity scores that can be derived from the self-report quantified TAND checklist.

Score name	Description	Maximum score	Proposed purpose
Individual item severity score (IISS)	TAND severity score of an individual item (eg, sleep)	10	Most useful to track an individual TAND manifestation of interest
Mean cluster severity score (CSS_mean_)	The arithmetic mean score of a specific TAND cluster (eg, autism-like cluster)	10	Most useful to compare one mean cluster score to another with the same maximum score of 10
Maximum cluster severity score (CSS_max_)	The arithmetic sum of all severity scores within a specific TAND cluster (eg, all 4 items in the scholastic cluster)	Maximum scores vary by cluster, given the varying number of items per cluster	Most useful to track the total severity of a specific cluster
Mean total TAND severity score (TTSS_mean_)	The arithmetic mean of all severity scores across all TAND clusters	10	Most useful to track or examine overall TAND severity
Maximum total TAND severity score (TTSS_max_)	The arithmetic sum of all severity scores across all TAND clusters	330^a^	Most useful to track or examine overall TAND severity

^a^The maximum will be 290 if question 6 (difficulties in school) is not completed for those of preschool age.

As part of the TANDem-1 study [19], the TAND-SQ was built into a smartphone app for ease of access, along with a TAND toolkit containing recommendations [22] on what additional help families might seek for TAND, and practical evidence-informed strategies they might implement themselves at home. On conclusion of the TANDem-1 project, the consortium acknowledged a number of scientific knowledge gaps that could be pursued as next steps. These included the need to consider how TAND severity may change over time, how caregiver well-being may be associated with TAND severity and severity trajectories, and the need to generate an evidence base to support the well-being of family caregivers in the TSC community.

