To begin exploring this question, we performed preliminary analyses of TAND severity over time using data from the TAND-SQ validation study [21], which included 21 repeat completions of the TAND-SQ. The checklists were completed with a mean age of 9.7 (SD 3.63; range 4-15) months apart. A total of 18 checklists were completed by caregivers of individuals with TSC reporting on their child (aged <18 years, n=12), or adult (aged >18 years, n=6) dependents, and 3 were individuals with TSC reporting for themselves. For analysis of change in TTSS_max_, we used the time of the second observation as integer months since the first observation (Table 1). Linear mixed-effects model fit by restricted maximum likelihood, including subject-specific random effects, showed that the mean TTSS_max_ was 100.5 (SD 64.2) at baseline, and that it changed by –1.05 units per month, equating to a 1% decline per month (10 units over 10 months or 12 units over 12 months). These findings therefore showed a “group-based” finding of gradual decline in the TTSS_max_ over time (Figure 1A), suggesting improvement in TAND severity over time. To explore the possibility of latent classes of change trajectories, we set a 10-unit change as a clinical marker of meaningful change (given that 10 units is the total of 1 severity quantification range per item). We grouped the 21 sets of observations into 3 groups based on whether trends between the 2 time points showed a decrease of >10 units, stayed within 10 units, or showed an increase of >10 units. We then regressed the TTSS_max_ per month, allowing for interaction with the 3 classes (stable, increasing, and decreasing). Results (Figure 1B) showed that 5 (24%) participants remained within 10 units from a relatively low baseline (T_0_ mean TTSS_max_ 52.6, SD 46.6), 5 (24%) participants had scores that increased by >10 units from a higher baseline (T_0_ mean TTSS_max_ 77.4, SD 70.0), and 11 (52%) participants had scores that reduced by >10 units from a high baseline (T_0_ mean TTSS_max_ 133.1, SD 63.2). These preliminary findings support the hypothesis of potential differential trajectories in TAND severity over time.

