### Data Analysis

#### Statistical Analysis Plan (Aim 1)

TAND severity will be quantified using the CSS_mean_ for each cluster and the TTSS_mean_/TTSS_max_ for overall TAND severity. These will be used to identify latent TAND severity trajectories using latent class mixed effect modeling [84]. The number of classes will be chosen based on statistical measures of model fit, the stability of the latent profiles, and the group sizes. Multinomial regression modeling [84] will be used to investigate the association of potential subject-specific covariates with the identified latent classes (predictors of TAND severity trajectories). All analyses will be done using R software (R Foundation for Statistical Computing) [85].

Power calculations are based on the estimation of the time trajectory and comparing different latent trajectories. Based on the data from the preliminary data analyses described earlier of 21 repeat TAND-SQs (42 observations), the power calculations were made in 2 ways. First, based on simulations [86] using a single slope (mean profile), power for sample sizes of n=500 and n=300 was calculated at a slope of -1.05% (power=100%/100%) and at –0.5% (power=97%/81%). Second, simulations were generated for n=500 and n=300 using a 3-trajectory solution with change in trajectories set at +1%, 0%, –1% (power=100%/100%), +0.5%, 0%, –0.5% (power=84%/72%), and 0%, +0.5%, +1% (power=86%/83%). Power calculations allowing for 3 different estimated baseline values of TTSS_max_ (75, 100, and 125) in addition to differing slopes for trajectories, show for n=500, 100% power (with 1% change in trajectories) and 93% power (with 0.5% change in trajectories). A sample size of n=300 using similar power calculations shows 100% power for 1% and 77% power for 0.5% differences in trajectory slopes.

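### TTSS_max sums 33 items, but 29 at preschool age, so a child who begins answering the school question in follow-up can only stay level or step up

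*Protocol article*

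**What the plan says.** Table 1 of the protocol article (section From TANDem-1 to TANDem-2) sets out the severity scores. The text before it says that "a 0-10 severity rating was added to all TAND cluster items". TTSS_max is "The arithmetic sum of all severity scores across all TAND clusters", with a listed maximum of 330. The table footnote says: "The maximum will be 290 if question 6 (difficulties in school) is not completed for those of preschool age". TTSS_mean is "The arithmetic mean of all severity scores across all TAND clusters", with a maximum of 10.

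Statistical Analysis Plan (Aim 1) carries both totals into the latent class mixed model: "TAND severity will be quantified using the CSS_mean_ for each cluster and the TTSS_mean_/TTSS_max_ for overall TAND severity". It does not choose between them.

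The inclusion criteria for Aims 1 and 2 let caregivers enrol for a person with TSC of any age. The Aim 1 hypothesis describes an accelerated longitudinal design with five time points, three months apart, over 12 months. The preliminary trajectories, and the power scenario with baselines of 75, 100 and 125, are on TTSS_max.

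**The concern.** A trajectory model reads a change in the outcome as a change in the person. TTSS_max can also change because more items are being added up. Items are scored from 0 upwards, so four newly answered items can only leave the sum level or raise it. The artefact therefore runs in one direction, towards the worsening trajectory that Aim 1 hypothesises.

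There is a between-person side as well. While a child is of preschool age, the ceiling is 290 and not 330. Equal severity per item then gives a lower total, which can distort classes defined partly by level and any association of class with age. The article lists age among the factors related to TAND severity, and an accelerated design depends on scores being comparable across ages.

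The plan already avoids the parallel problem for clusters. Table 1 notes that cluster sums have differing maxima, and the Aim 1 analysis uses only the cluster mean. For the total, it keeps the raw sum as an option.

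**Working it through.** **Inputs from the protocol article**
- Item range 0 to 10, and ceilings of 330 and 290 (Table 1 and the text before it).
- Scholastic cluster: "all 4 items in the scholastic cluster" (Table 1).
- Preliminary data on 21 people: "the mean TTSS_max_ was 100.5 (SD 64.2) at baseline". The change was –1.05 units per month. The baseline means of the three preliminary groups were 52.6, 77.4 and 133.1 (section Longitudinal Trajectories of TAND Severity and Their Potential Predictors).
- Visits at months 0, 3, 6, 9 and 12.
- Power simulations with trajectories of +1%, 0% and –1% (Statistical Analysis Plan, Aim 1).

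**Not given, so assumed:** the average rating r of the four school items in children who start answering them. The working value is the overall item mean, and the possible range is 0 to 10. The number of such children is also not given, and no value is assumed for it.

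**Step 1: reproduce the plan's figures.** 330/10 = 33 items and 290/10 = 29 items. 330 – 4 × 10 = 290, which matches the four scholastic items exactly. The stated 1% decline also reproduces: 1.05/100.5 = 1.04% per month.

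**Step 2: ceiling.** 29/33 = 0.879, so the preschool ceiling is about 12% lower.

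**Step 3: step in TTSS_max when question 6 starts to be answered.** Step = 4r.
- r = 100.5/33 = 3.05 gives 12.2 points. Reading 100.5 as a 29-item score gives 4 × 100.5/29 = 13.9.
- r from 0 to 10 gives 0 to 40 points.
- With r set to the item mean at each preliminary group baseline:

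| Baseline TTSS_max | Step, 33-item basis | Step, 29-item basis |
|---|---|---|
| 52.6 | 6.4 | 7.3 |
| 77.4 | 9.4 | 10.7 |
| 133.1 | 16.1 | 18.4 |

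The step passes 10 units only if r exceeds 10/4 = 2.5.

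**Step 4: slope produced by a pure step.** Least squares over the five visits uses deviations from month 6 of –6, –3, 0, 3 and 6, with sum of squares 90.
- Step first seen at month 3 or month 12: slope = (6/90) × step = 0.067 × 12.2 = +0.81 units per month.
- Step first seen at month 6 or month 9: slope = (9/90) × step = 0.10 × 12.2 = +1.22 units per month.

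For comparison, +1% of a baseline near 100 is about +1 unit per month.

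**Step 5: the same event on TTSS_mean over answered items.** With the other 29 items at mean m = 3.05, change = (29m + 4r)/33 – m = 4(r – m)/33.
- r = m: 0.00.
- r = 0: –0.37.
- r = 10: +0.84.

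**The case against.** The strongest reply has four parts.

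**The size is assumed.** About 12 points is not a figure in the article. It gives the school items the item mean of 21 people, a mix of children, adult dependents and self-reporters. At the baseline of the low-scoring group the step is about 6 to 7 points. Relative to the baseline SD it is 12.2/64.2 = 0.19. This stands, and the figure has to carry its assumption and its range.

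**The 10-unit threshold is not in the planned analysis.** In the preliminary work, "we set a 10-unit change as a clinical marker of meaningful change" was the basis for grouping 21 pairs of observations. The main analysis chooses latent classes by model fit, stability of the profiles and group sizes. A reader might infer that a step above 10 units places a child in the worsening class. The article does not support that.

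**Few children may be affected.** Only those who begin answering question 6 within their own 12 months show the step. Their number is unknown, and nothing shows that they would form or distort a class among 500. This also stands.

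**The plan already includes the better score.** TTSS_mean is named, the article reports validity evidence for it, and the changed maximum is disclosed. A condensed article may also leave item scoring to the full plan. This answers the point only in part. The article itself names the raw sum as a trajectory outcome while stating that its item count varies, and it gives neither score priority.

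One could go further and say that TTSS_max adds nothing beyond the artefact. That is too strong. The exact factor of 33 needs all items answered, and TTSS_max links the results to the preliminary and power figures.

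**Conclusion.** The defect in TTSS_max holds. Followed as written, one of the two named overall outcomes can rise in a child whose other 29 ratings have not moved, and it has a ceiling about 12% lower at preschool age. The item counts are exact.

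The size is conditional. It is about 12 points if school items are rated like the rest, about 6 to 18 across the preliminary group baselines, and 0 to 40 arithmetically. At 12.2 points the fitted slope is +0.81 to +1.22 units per month, similar to the +1% trajectory used in the power simulations.

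A reader might infer that starting school will create a spurious worsening class. The article does not show that, because it gives neither the school-item ratings nor the number of children changing status. What is established is a risk of misclassifying those children and of distorting level classes and the age association. TTSS_mean largely removes the step but does not guarantee zero change if school items differ from the rest. This is a cheap improvement.

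**What to change.** 1. Name TTSS_mean, not TTSS_max, as the overall-severity outcome for the Aim 1 trajectory model.
2. Hold the item set constant within person: the 29 non-school items at every wave for anyone of preschool age at any wave, and 33 items otherwise.
3. Add an analysis on the common 29 items for all participants. Step 2 alone still leaves some people scored on 29 items and others on 33; the common set removes that between-person difference.
4. If TTSS_max is kept to link to the planning figures, report it on the fixed item set or as 33 × TTSS_mean.

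The cost is scoring code and a sentence or two in the analysis plan. Data collection does not change, and the primary outputs for Aims 1 and 2 are not expected until July 2028. The downside is that school items drop out of the total score for the children who change status. They can still be analysed through the scholastic cluster score.

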### Longitudinal Trajectories of TAND Severity and Their Potential Predictors

At present, there are almost no data about the natural trajectory of the severity of TAND manifestations over time, and this has been identified as an important area for TAND research [15]. There is a small body of literature related to autism, social-communication development, and behavior in TSC, where studies have investigated the 0-36 months age group in relation to biomarkers for autism [23-25]. In earlier studies, the Tuberous Sclerosis Registry to Increase Disease Awareness (TOSCA) consortium [26] examined TAND manifestations stratified by age (children vs adults), and across 7 age bands [12]. Many significant differences were observed with higher rates of TAND manifestations in children vs adults [12]. However, on further examination of age-based profiles in relation to intellectual ability (IA)—known to be a strong correlate of many neuropsychiatric features—results were significantly different [27]. Once controlled for IA, children had higher rates of overactivity, but most behavioral difficulties were higher in adults. At the psychiatric level, rates of attention-deficit/hyperactivity disorder (ADHD) were higher in children, but anxiety and depressive disorders were higher in adults. Controlling for IA, males had higher rates of overactivity and impulsivity as well as ADHD and autism. Importantly, no genotype-TAND correlations were seen on any behavioral, psychiatric, or academic manifestations after controlling for IA [27]. These findings were a stark reminder of the limitations of cross-sectional correlations of TAND and the need for a standardized and quantified tool that can measure change in severity over time.

Apart from the clear research evidence of high levels of heterogeneity in TAND profiles between individuals with TSC, there is also clinical evidence of significant interindividual and intraindividual variability in those outcome patterns over time. However, the majority of TSC studies to date (including clinical trials in TSC) have “averaged out” those health outcomes across study samples or in prespecified stratified subgroups of individuals (eg, Examining Everolimus in a Study of Tuberous Sclerosis Complex-1, 2, and 3) [28-31]. Therefore, describing populations of individuals with TSC using averaged estimates leads to the risk of oversimplifying the complex interindividual and intraindividual variability of real-life TSC [32]. For example, in any intervention, an assumption is typically made that the outcome variable of interest is relatively stable over time and that the statistical change observed will be attributable to the “active ingredient” of the intervention. However, it is likely that there will be naturalistic changes in many outcomes over time. These changes may be associated with differential trajectories of groups of individuals. In the case of TAND, it is very important to consider changes in severity over time, given that TAND severity is highly variable. While it may present a stable ”mean” trajectory, it may be associated with differential natural trajectories over time. Understanding the natural longitudinal TAND severity trajectory of individuals with TSC and identifying differential trajectories of TAND severity over time are fundamental aspects for TAND intervention research.

To begin exploring this question, we performed preliminary analyses of TAND severity over time using data from the TAND-SQ validation study [21], which included 21 repeat completions of the TAND-SQ. The checklists were completed with a mean age of 9.7 (SD 3.63; range 4-15) months apart. A total of 18 checklists were completed by caregivers of individuals with TSC reporting on their child (aged <18 years, n=12), or adult (aged >18 years, n=6) dependents, and 3 were individuals with TSC reporting for themselves. For analysis of change in TTSS_max_, we used the time of the second observation as integer months since the first observation (Table 1). Linear mixed-effects model fit by restricted maximum likelihood, including subject-specific random effects, showed that the mean TTSS_max_ was 100.5 (SD 64.2) at baseline, and that it changed by –1.05 units per month, equating to a 1% decline per month (10 units over 10 months or 12 units over 12 months). These findings therefore showed a “group-based” finding of gradual decline in the TTSS_max_ over time (Figure 1A), suggesting improvement in TAND severity over time. To explore the possibility of latent classes of change trajectories, we set a 10-unit change as a clinical marker of meaningful change (given that 10 units is the total of 1 severity quantification range per item). We grouped the 21 sets of observations into 3 groups based on whether trends between the 2 time points showed a decrease of >10 units, stayed within 10 units, or showed an increase of >10 units. We then regressed the TTSS_max_ per month, allowing for interaction with the 3 classes (stable, increasing, and decreasing). Results (Figure 1B) showed that 5 (24%) participants remained within 10 units from a relatively low baseline (T_0_ mean TTSS_max_ 52.6, SD 46.6), 5 (24%) participants had scores that increased by >10 units from a higher baseline (T_0_ mean TTSS_max_ 77.4, SD 70.0), and 11 (52%) participants had scores that reduced by >10 units from a high baseline (T_0_ mean TTSS_max_ 133.1, SD 63.2). These preliminary findings support the hypothesis of potential differential trajectories in TAND severity over time.

